## Revision History

| Protocol Version | Date       | Amendments                                                                                                                                                                                                                                                                                                                                                                                                                                                                                                                                                                                                                                                                                                                                                                                                                                                                                                                                                                                                                                                                                                                     |
|------------------|------------|--------------------------------------------------------------------------------------------------------------------------------------------------------------------------------------------------------------------------------------------------------------------------------------------------------------------------------------------------------------------------------------------------------------------------------------------------------------------------------------------------------------------------------------------------------------------------------------------------------------------------------------------------------------------------------------------------------------------------------------------------------------------------------------------------------------------------------------------------------------------------------------------------------------------------------------------------------------------------------------------------------------------------------------------------------------------------------------------------------------------------------|
| V 2.0            |            | 
Change of Senior statistician to [name] (Pg 2/3)
 
Update to allow recruitment from non-NHS sites (Pg 21, 31) and 'An additional sensitivity analysis of NHS-only patients (including patients referred by their GPs to non-NHS sites) will be conducted to ensure generalisability to a NHS population.', Pg 31)
 
Clarify that full lower limb ultrasound is bilateral and includes groin to ankle (Pg 26/27)
 
Clarify that both above and below knee stockings are allowed and duration of use is as per local policy (Pg 24)
 
Clarify that confirmation of VTE by imaging is required if patient self reports a VTE (Pg 27)
 
Clarify that 'Recruitment will continue while the interim data is analysed.' (Pg 31)
 
Addition of section to detail the collection of protocol deviations and violations and serious breaches (Pg 38)
 
The correction of typographical errors (<math>\geq 18</math> years, Pg 20), EDTPT post discharge, Pg 24), removal of 'witnessed' for verbal consent, Pg 25), ('since last contact Pg 27), Addition of 'randomisation' Pg 38)
 |
| V 1.0            | 30/11/2023 | Protocol approved by the REC                                                                                                                                                                                                                                                                                                                                                                                                                                                                                                                                                                                                                                                                                                                                                                                                                                                                                                                                                                                                                                                                                                   |

## **Funder**

This study is funded by the National Institute for Health Research (NIHR) Health Technology Assessment programme (NIHR155294). The views expressed are those of the author(s) and not necessarily those of the NIHR or the Department of Health and Social Care.

This protocol describes the GRACE study and provides information about procedures for entering participants. Every care was taken in its drafting, but corrections or amendments may be necessary. These will be circulated to investigators in the study. Problems relating to this study should be referred, in the first instance, to the Chief Investigator.

This study will adhere to the principles outlined in the UK Policy Frame Work for Health and Social Care Research. It will be conducted in compliance with the protocol, the Data Protection Act and other regulatory requirements as appropriate.

## GLOSSARY OF ABBREVIATIONS

|           |                                                                                                                 |
|-----------|-----------------------------------------------------------------------------------------------------------------|
| CI        | Confidence Interval                                                                                             |
| CTU       | Clinical trials unit                                                                                            |
| DHRA tool | Department of health risk assessment tool                                                                       |
| DOAC      | Directly acting Oral AntiCoagulants                                                                             |
| DVT       | Deep venous thrombosis                                                                                          |
| EDPTP     | Extended duration pharmacological thromboprophylaxis                                                            |
| GAPS      | Graduated compression stockings as adjuvant to pharmaco-thromboprophylaxis in elective surgical patients' study |
| GCS       | Graduated compression stocking                                                                                  |
| HAT       | Hospital-acquired thrombosis                                                                                    |
| ICC       | Intraclass correlation                                                                                          |
| iDMC      | Independent data monitoring committee                                                                           |
| LMWH      | Low-molecular weight heparin                                                                                    |
| NHS       | National Health Service                                                                                         |
| NICE      | National Institute for Health and Care Excellence                                                               |
| PE        | Pulmonary embolism                                                                                              |
| PPI       | Patient and public involvement                                                                                  |
| PTS       | Post-thrombotic syndrome                                                                                        |
| RCT       | Randomised Controlled Trial                                                                                     |
| RGIT      | Research Governance and Integrity Team                                                                          |
| TEDS      | Thromboembolic deterrent stockings                                                                              |
| SAP       | Statistical Analysis Plan                                                                                       |
| SMS       | Short Messaging Service                                                                                         |
| SOP       | Standard operating procedure                                                                                    |
| TSC       | Trial Steering Committee                                                                                        |
| VTE       | Venous thromboembolism                                                                                          |
| WHO       | World Health Organisation                                                                                       |

## STUDY SUMMARY

**TITLE** Graduated Compression stocking as an adjunct to Extended duration pharmacological thromboprophylaxis for venous thromboembolism prevention – the GRACE multi-centre randomised controlled trial

**TRIAL DESIGN** Assessor-blinded randomised controlled trial with a non-inferiority comparison

**AIMS** To evaluate the potential benefit of Graduated Compression Stockings (GCS) in addition to extended duration pharmacological thromboprophylaxis (EDPTP) for elective surgical patients at highest risk of venous thromboembolism (VTE)

**OUTCOME MEASURES** Primary Outcome:  
Imaging-confirmed lower limb DVT with or without symptoms, or PE with symptoms, occurring up to 90 days post-surgery.

Secondary outcomes up to 90 days:

- Mortality
- Adverse events with GCS
- Adherence with GCS
- Adherence with EDPTP
- Safety outcome measures

**POPULATION** Adults undergoing surgical procedures requiring extended duration thromboprophylaxis measures as described by NICE.

**SAMPLE SIZE** 8,608 participants from approximately 50 sites.

**PATIENT ELIGIBILITY** Inclusion criteria

- Adults (≥18 years of age)
- Participants undergoing elective surgery; risk assessed as requiring EDPTP

Exclusion criteria

- Contraindications to EDPTP or GCS\*
- Individuals requiring therapeutic anticoagulation e.g., anticoagulation for previous DVT
- Known thrombophilia or thrombogenic disorder

*\*antiplatelet therapy e.g. aspirin is not an exclusion*

**DURATION** 39 months (6 months set-up; 24 months recruitment; 3 months follow-up; 6 months close-down)

## 1. INTRODUCTION

### 1.1. BACKGROUND

Hospital-acquired thrombosis (HAT) is defined as any venous thromboembolism (VTE) during admission and within 90 days of hospital discharge (1), and is a term that encompasses both deep vein thrombosis (DVT) and pulmonary embolism (PE). It is estimated that as many as 60% of all VTE cases are hospital related (2). HAT represents a significant cause of preventable mortality, with around 60.4 deaths from VTE per 100,000 hospital admissions reported in the year 2020-2021 within the NHS (1) – equivalent to around 12,300 people dying each year from hospital-caused VTE, which is 10-fold higher than the number dying from road traffic accidents. The UK annual VTE-related mortality prior to implementation of a national programme of thromboprophylaxis, was estimated to be up to 32,000 fatalities, with associated costs as high as £640 million per annum (3).

VTE is a significant cause of long-term disability with subsequent societal and economic consequences (4). Morbidity following a DVT is substantial, with as many as 50% of patients developing post thrombotic syndrome (PTS) (5), characterised by troubling chronic leg pain, oedema, and venous skin changes (6). Crucially, the severity of chronic venous disease is much worse in those with PTS in comparison to primary venous disease and the rate of venous ulceration is as high as 29% (7). Those with PTS have a significantly worse quality of life, which is comparable to those with cancer and congestive heart failure (8, 9). Furthermore, PE is associated in some with life-long functional, physiological and psychological harm (10, 11). Ultimately, PE can cause death during the index event and in an estimated 2% can be complicated by chronic thromboembolic pulmonary hypertension, resulting in chronic pulmonary hypertension and heart failure (12, 13). Persistent cardiac insufficiency have been reported in as many as 13.2% of PE cases (11).

Surgery is a significant risk factor for VTE, with those undergoing lower extremity orthopaedic operations, major oncological surgery or pelvic surgery being at the highest risk (14, 15). Previous studies report the risk of untreated high-risk surgical

patients developing HAT is as high as 40-60% in elective joint replacement and 15-40% in general surgery patients (14, 16). For these patients at highest risk of VTE, the prevention strategies include extended pharmacological thromboprophylaxis (EDPTP) prescribed beyond the hospital stay and provision of graduated compression stockings (GCS). National Institute for Health and Care Excellence (NICE) [NG89] guidelines recommends certain cohorts of surgical patients should receive mechanical thromboprophylaxis, most commonly in the form of GCS, in addition to the EDPTP (17). This cohort encompasses patients undergoing orthopaedic surgery with ongoing lower limb immobilization including elective hip replacement surgery (EDPTP for 28-38 days post-surgery) and elective knee replacement surgery (EDPTP for 14 days post-surgery) in addition to those undergoing major cancer surgery in the abdomen or pelvis (EDPTP for 28 days post-surgery) (17).

However, it is currently unclear if GCS provide additional benefit to EDPTP in this cohort. Recent studies have called this practice into question, the NIHR-funded Graduated compression as an Adjunct to Pharmacoprophylaxis in Surgery (GAPS) trial demonstrated that inpatient pharmacological thromboprophylaxis was non-inferior to inpatient pharmacological thromboprophylaxis in addition to GCS for surgical inpatients deemed to be at medium-high risk of VTE (18). For those requiring EDPTP, there is insufficient evidence to support the provision of GCS. There is uncertainty for healthcare professionals and current practice is potentially leading to avoidable complications and significantly increased NHS costs.

## **1.2. RATIONALE FOR CURRENT STUDY**

There is currently no high-quality evidence to support the use of GCS in addition to EDPTP in patients deemed to be at the highest risk of VTE. A Cochrane Review (19) which reported benefit for GCS included small trials (18-440 patients), only one of which was published this millennium (20), and many of these trials were funded by stocking manufacturers.

Additionally, two large recent trials were excluded from this review in stroke and orthopaedic patients - neither study supported the use of GCS (21, 22). Furthermore,

as noted above, the GAPS trial reported that pharmacological thromboprophylaxis alone is non-inferior to pharmacological thromboprophylaxis and GCS (18). This proposal includes individuals requiring EDPTP, at highest risk, who were excluded from GAPS, hence the results cannot be directly extrapolated (18).

In preparation for this bid, a systematic review and meta-analysis of VTE rates in surgical patients treated with pharmacological thromboprophylaxis in addition to GCS in comparison to pharmacological thromboprophylaxis alone was undertaken in accordance with PRISMA guidelines (23) and following a registered protocol (CRD42017062655), accepted for publication in *Annals of Surgery*). Online searches of the MEDLINE and EMBASE databases were performed returning randomised trials and trial arms reporting the rate of VTE after any surgical procedure, utilising pharmacological thromboprophylaxis alone or pharmacological thromboprophylaxis in addition to GCS. Individual rates of deep venous thrombosis (DVT), pulmonary embolism (PE), and VTE-related mortality were pooled via fixed and random effects models. Clinicaltrials.gov, European Union Clinical Trials, International Standard Randomised Controlled Trial Number Registry were also searched for active trials in this area. This review concluded “no significant differences in rates of DVT, PE and VTE-related mortality between pharmacological prophylaxis alone versus pharmacological prophylaxis with additional GCS”. Subgroup analysis of surgical patients treated with EDPTP pooling data from 27 trial arms was undertaken. When pooling 24 study arms reporting EDPTP alone, including 10,187 participants, the rate of DVT was 10.97%. Analysis of 3 study arms reporting EDPTP in addition to GCS, pooling 651 participants, demonstrated a DVT rate of 7.37%. A single RCT directly comparing EDPTP alone vs EDPTP in addition to GCS reported rates of VTE of 4.8% and 5.5% respectively (OR 0.88, 95% CI: 0.46-1.65,  $p = 0.69$ ). However, this study reported symptomatic VTE only, and is consequently under powered, hence the lower reported numbers in comparison to screen detected DVT in the aforementioned pooled trial arms. Overall, the additional benefit of GCS is not clear based on existing data.

Highlighting the importance of VTE, NICE alongside the Commissioning for Quality and Innovation (CQUIN), have prioritised VTE reduction strategies over the last decade (24). National initiatives have made VTE risk assessment, such as the Department of Health risk assessment tool (DoH RAT), and subsequent prescription of thromboprophylaxis, routine practice resulting in 96% VTE risk assessment compliance for adult inpatients by 2013 (17, 25). Hence, VTE risk assessment is now an integral part of routine clinical practice, however, there is a lack of high-quality evidence to guide subsequent thromboprophylaxis strategies employed based on these mandated risk assessments. Our detailed feasibility survey revealed that there are currently two established practices within the NHS: those that prescribe additional EDPTP with additional GCS and those that prescribe EDPTP alone.

We undertook a review of the Hospital Episode Statistics data and ascertained that ~270,000 procedures requiring EDPTP are undertaken each year within the NHS (26). The cost of purchasing and applying GCS equates to a minimum of £31.05 per patient episode (18, 27). Based on our evaluation, the costs of GCS on conservative figures for those requiring EDPTP is a minimum of £8.3 million per year. In addition to the financial cost, GCS are burdensome for patients, with complication rates of up to 5%, including discomfort, ulceration, rashes, formation of a constrictive band, ischaemia and abrasions (21, 28). GCS may also pose a falls hazard given their synthetic material construction (29).

With increasing efficiency savings required, we need clear evidence to justify the huge financial resource allocated to GCS. Furthermore, if GCS were to offer benefit in VTE prevention over and above that afforded by EDPTP, this would need to be weighed against their risks and disadvantages.

## 2. STUDY OBJECTIVES

To evaluate the VTE rates with or without the use of Graduated Compression Stockings (GCS) in addition to giving blood thinning medication post discharge from hospital for surgical patients at highest risk of venous thromboembolism (VTE).

The secondary aims are to determine any difference in adverse events and mortality with or without GCS use.

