## **2.2 SECONDARY OUTCOMES**

Secondary outcomes will be defined as occurring within 90 days of surgery.

- Mortality
- Adverse events related to GCS
- Adherence with GCS\*
- Adherence with EDPTP
- Safety outcome measures

\*Adherence will be assessed in comparison to the advice provided by the local clinical team at the time of discharge i.e., if advised to wear GCS every day for the full duration of extended thromboprophylaxis, then this timepoint will be the level of full compliance for comparison. However, if participants are advised to wear GCS whilst an inpatient only, then this will be used as the level of full compliance.

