### **Day 7 post procedure**

Day 7 post procedure (data collected via telephone or online survey [link to survey sent via email or SMS])

- VTE outcome (participants will be asked to report on whether or not they have been diagnosed with a DVT or PE within the past 7-days)
- Adverse events associated with GCS will be captured (for those enrolled in the control arm)
- Participant reported adherence to GCS (for those enrolled in the control arm)
- Adherence to EDPTP

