## **7.2. REPORTING PROCEDURES**

For the purposes of the study, only AEs related to the study intervention (graduated compression stockings) will be recorded. This information will be collected at 7-days, between 21 and 35 days and at 90 days.

Safety monitoring includes any adverse events with GCS or bleeding events with the standard of care pharmacological thromboprophylaxis. Major bleeding will be defined as per the International Society on Thrombosis and Haemostasis definition (36).

Participants who report a treatment related AE which requires further investigation/follow-up will be advised to consult with their GP/relevant clinical team where necessary. Depending on the nature of the event the reporting procedures below should be followed. Any questions concerning adverse event reporting should be directed to the Chief Investigator in the first instance.

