### **7.2.2 Serious AEs**

An SAE form should be completed and emailed to the Chief Investigator within 24 hours. However, hospitalisations for elective treatment of a pre-existing condition do not need reporting as SAEs.

All SAEs should be reported to the Research Ethics Committee where in the opinion of the Chief Investigator, the event was:

- 'related', ie resulted from the administration of any of the research procedures; and
- 'unexpected', ie an event that is not listed in the protocol as an expected occurrence

Reports of related and unexpected SAEs should be submitted within 15 days of the Chief Investigator becoming aware of the event, using the NRES SAE form for non-IMP studies. The Chief Investigator must also notify the Sponsor of all related and unexpected SAEs.

Local investigators should report any SAEs as required by their Local Research Ethics Committee, Sponsor and/or Research & Development Office.

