## Appendix 1. Summary of investigations, treatment and assessments

| Assessment                                                                        | Days of assessment     |                      |   |          |    |
|-----------------------------------------------------------------------------------|------------------------|----------------------|---|----------|----|
|                                                                                   | Pre-surgical procedure | 0 (Day of procedure) | 7 | 21 to 35 | 90 |
| Inclusion/Exclusion                                                               | X                      | X                    |   |          |    |
| Informed consent                                                      | X                      |                      |   |          |    |
| Screening assessments                                                             | X                      |                      |   |          |    |
| Demographics                                                          |                        | X                    |   |          |    |
| Medical history (including concurrent medications)                    |                        | X                    | X | X        |    |
| Provision of leaflet explaining the signs and symptoms of developing a blood clot | X                      |                      |   |          |    |
| Provision of stockings*                                                           |                        | X                    |   |          |    |
| VTE outcome (self-reported)                                                       |                        |                      | X | X        | X  |
| A full lower limb deep venous thrombosis scan                                     |                        |                      |   | X        |    |
| Adverse Events Assessment*                                                        |                        |                      | X | X        | X  |
| Adherence to GCS*                                                                 |                        |                      | X | X        | X  |
| Adherence to EDPTP                                                                |                        |                      | X | X        | X  |

\*Patients randomised to the control arm only

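### A between-arm difference in adverse events is a stated secondary aim, but scheduled adverse event collection covers the stocking arm only, and no contact collects bleeding in either arm

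*Protocol*

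**What the plan says.** Protocol section 2 sets a comparative aim: "The secondary aims are to determine any difference in adverse events and mortality with or without GCS use". Section 2.2 lists a narrower outcome, "Adverse events related to GCS", and, as separate items, mortality and safety outcome measures that it does not define.

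Collection is set out in three places:

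- Section 5.3 has the same item at day 7, days 21 to 35 and day 90: "Adverse events associated with GCS will be captured (for those enrolled in the control arm").
- In Appendix 1 the Adverse Events Assessment row is starred, and the footnote reads "Patients randomised to the control arm only".
- Section 7.2 states that "only AEs related to the study intervention (graduated compression stockings) will be recorded", and section 7.2.1 repeats this for non-serious events.

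On bleeding, section 7.2 says: "Safety monitoring includes any adverse events with GCS or bleeding events with the standard of care pharmacological thromboprophylaxis". It adopts the ISTH definition of major bleeding. For serious events, section 7.2.2 says "An SAE form should be completed and emailed to the Chief Investigator within 24 hours", with no limit to one arm. Section 5.3 captures 90-day mortality, also without such a limit.

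**The concern.** A difference between arms needs the same question put to both arms. Here one arm is asked three times and the other never.

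Section 1.2 lists the harms expected of stockings as discomfort, ulceration, rash, a constrictive band, ischaemia and abrasion, and names falls separately. Apart from the constrictive band, most of these can also occur after joint replacement or major abdominal surgery in a patient without stockings. A count from the stocking arm alone, reported by participants who know their allocation and filtered by whether the event is put down to the stocking, cannot separate stocking harm from what surgery produces anyway.

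At stake is the harm side of the trial's message. Section 1.2 says that any benefit of stockings would have to be weighed against their disadvantages, and section 11 lists an understanding of stocking safety among the outputs. Bleeding matters for the same reason: it is declared part of safety monitoring, but the schedule gives it no place.

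**Working it through.** **The plan's own figures (background only).** The protocol gives no figure for the adverse event comparison, so its sample size serves only to fix the numbers per arm.

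- Inputs from section 6.1: 8% in both arms, margin 2%, one-sided 2.5%, power 90%.
- n per arm = (1.960 + 1.2816)² × 2 × 0.08 × 0.92 / 0.02² = 3,867, so 7,734 in total (stated: 7,736).
- With 4% missing: 8,264 / 0.96 = 8,609 after rounding up (stated: 8,608).
- Both agree to rounding. The step from 7,736 to 8,264 for the interim analyses is taken as stated.
- Per arm: 8,608 / 2 = 4,304 randomised; 8,264 / 2 = 4,132 after the missing-data allowance.

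**What is collected, by arm.**

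| Item | EDPTP + GCS | EDPTP alone |
|---|---|---|
| Scheduled adverse event assessment (5.3, Appendix 1) | 3 contacts, GCS-associated only | 0 contacts |
| Scheduled bleeding item (5.3, Appendix 1) | none | none |
| SAE form (7.2.2) | yes | yes |
| Mortality to day 90 (5.3) | yes | yes |
| VTE and EDPTP adherence questions (5.3) | 3 contacts | 3 contacts |

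The first row decides the point. Section 6.2 analyses secondary outcomes with generalised linear models in the manner of the primary outcome, but a treatment effect cannot be fitted to data from one arm. EDPTP-alone participants who wear stockings anyway also have no scheduled assessment. The last row shows that the EDPTP-alone arm is already contacted at all three times.

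**What the one-arm count leaves open.** Take the upper complication rate of 5% from section 1.2 as the control-arm rate. The documents give no rate for the same kinds of event without stockings, so assume 0% to 5%. The true difference then lies anywhere from 5 to 0 percentage points. The control-arm proportion would itself be precise, at 1.96 × √(0.05 × 0.95 / 4,304) = 0.65 points either side, but that precision says nothing about where in the range the difference lies.

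**What asking both arms would give.** Half-width = 1.96 × √[(p₁(1 − p₁) + p₂(1 − p₂)) / n], with p₁ = 5% and n = 4,132:

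- p₂ = 2%: 1.96 × √[(0.0475 + 0.0196) / 4,132] = 0.79 points
- p₂ = 5%: 1.96 × √[(0.0475 + 0.0475) / 4,132] = 0.94 points

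**Bleeding.** Section 7.2 names bleeding as monitored but also says that only stocking-related events are recorded. A bleed on pharmacological prophylaxis is not a stocking-related event. One that meets a seriousness criterion can go on the SAE form. A non-serious one has no clear route in either arm.

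**The case against.** The best defence is that the outcome list, the three contacts, the reporting rules and the schedule all describe stocking-related events, and that the sentence in section 2 is the outlier. On that view the aim is loosely worded and the collection is as intended. This is a fair reading, and it shows that restating the aim would also remove the contradiction. It does not show that the aim as written can be met.

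It can also be said that some harms, such as a constrictive band, are specific to stockings, so a stocking-arm rate is informative without a comparator. That stands for those harms, but not for rash, skin damage, discomfort or falls.

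A reader might go further in four ways that the documents do not support:

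- *That the EDPTP-alone arm yields no adverse event data.* The SAE form and mortality capture apply to both arms. What is missing is scheduled assessment, and with it non-serious events.
- *That bleeding in the EDPTP-alone arm has no route.* Serious bleeds can be reported as SAEs, and section 2.2 keeps safety outcomes as a separate item. The gap in scheduled collection is the same in both arms, because the control-arm item is also limited to stocking-associated events.
- *That the count overstates stocking harm by the whole background rate.* Attribution removes some background events, so the background rate is an upper limit. The documents give no basis for sizing the actual bias.
- *That the case for omitting stockings fails.* It rests on VTE non-inferiority, and section 1.2 also argues from cost.

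**Conclusion.** The contradiction stands. If the protocol is followed exactly, the between-arm difference in non-serious adverse events cannot be estimated, and an analysis plan cannot supply data that were never collected. The mortality half of the aim is unaffected. Scheduled bleeding collection is unspecified in both arms, and the route for non-serious bleeding is unclear.

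The size is best put as a loss of information: a difference that the trial could estimate to within about 0.8 to 0.9 points is instead left undetermined. Those figures assume a 5% rate with stockings (the protocol's upper value), an assumed 2% to 5% without, and the same 4% loss as for the primary outcome. The finding itself does not depend on them.

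This should be fixed, but it does not threaten the trial's main conclusion: the primary endpoint, margin, sample size and stopping rules are untouched.

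**What to change.** Preferred change:

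- At the three existing contacts, ask both arms the same short list, whatever the presumed cause: leg skin problems, discomfort, falls, limb ischaemia and bleeding.
- Remove the asterisk from the Adverse Events Assessment row in Appendix 1. It should stay on stocking provision and stocking adherence.
- Align sections 2.2, 5.3, 7.2 and 7.2.1 with this, and state how bleeding, including non-serious bleeding, is recorded. Section 7.2 should also stop calling stockings the study intervention, since section 5.1.1 makes EDPTP alone the intervention arm.
- Analyse each item as a between-arm difference with its confidence interval. Keep events attributed to stockings as a description of the control arm.

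The cost is an amendment, a few extra survey items for about 4,300 EDPTP-alone participants, a bleeding item for the control arm, and the handling of the answers. No visit is added. Contacts completed before the change cannot be reliably recovered, so the comparison would rest on participants asked under the new wording.

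If this is not done, restate the aim in section 2 as describing stocking-related adverse events in the stocking arm only, and keep the comparison for mortality. That costs only wording, but it gives up the comparative safety aim, and the bleeding route in section 7.2 would still need to be settled.
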